#### Clinical assessments

##### Modified Ashworth Scale

The Modified Ashworth Scale (MAS) is widely used to evaluate muscle spasticity by measuring resistance during passive soft-tissue stretching. The MAS has a six-point scale (ranging from 0 to 4, respectively 0, 1, 1^+^, 2, 3, 4) with a score of 0 representing no spasticity and a score of 4 representing severe spasticity (34, 35). An experienced clinician will use MAS to evaluate the muscle tone of the elbow flexor, elbow extensor, and wrist flexor and extensor on the hemiplegic side of the patient and record them, respectively.

##### Fugl-Meyer Assessment of Upper Extremity Scale

We will also assess the mean change in the Fugl-Meyer Assessment of the Upper Extremity (FMA-UE) Scale. This is an assessment table for the upper extremity, upper arm, and wrist/hand, which examines motion, coordination, and reflexes. The FMA-UE scale has three points (respectively, 0, 1, 2 score, 0 is the worst, 2 is the best) for each item with a maximum of 66 points. It is widely used to measure post-stroke motor recovery of the upper limb because of its convenience, effectiveness, and reliability, and the higher the score, the greater the motor function (36, 37). Some of the recent refinement of flexor or extensor synergy movements and out-of-synergy movements based on the movements assessed in FMA-UE will help reflect changes in motor innervation pathways through score changes (9).

Those clinical assessments will be performed at baseline, after 4 weeks of treatment, and at follow-up.

#### Neurophysiological examinations

##### CST excitability: Motor evoked potential

TMS evoked neurophysiological parameters are useful measures for monitoring post-stroke patients and predicting recovery of motor function (38). MEP is used to investigate CST activities frequently. In this study, we will collect the contralesional hemisphere's resting motor threshold (rMT) and motor evoked potentials (MEP) from the first dorsal interosseous (FDI) muscles. All subjects will be seated in a comfortable chair with their hands completely relaxed during the evaluations. The transcranial magnetic stimulation coil will be held tangentially in a posterior anterior plane at a 45° angle from the midline over the hotspot. As mentioned before, we will primarily find the hot spots of FDI, and measure rMT. After that, MEPs will be sampled during TMS at 110% rMT and will be kept constant during the following evaluations. We will record the MEP as zero if it cannot be evoked (39).

##### RST excitability: Startle reflex

The subject will be instructed to sit in a chair with a backrest, with the hands resting on the thighs and remaining relaxed. Two pairs of surface electromyography electrodes were applied to the left and right sternocleidomastoid muscles (SEM) belly record muscle response. After wearing a headphone (Sennheiser HD25-I; Wedemark, Germany), the subjects will receive a total of 30 sound stimuli. Half of them are 40 ms beeps at 80 dB and half are 40 ms white noises at 120 dB. The stimulus firing sequence was randomly generated, with a random interval of 6–10 s between stimuli to ensure subjects were fully relaxed. The Psychtoolbox-3 toolkit within MATLAB (2017b, MathWorks, Natick, MA, USA) will be used for the design and execution of this trial. The sEMG signals will be collected by the Ultimu EMG system (Noraxon USA Inc., Scottsdale, AZ, USA) at a sampling rate of 2,000 Hz. Raw sEMG data will be output and processed under the same software. It will be segmented, bandpass filtered at 30–300 Hz, and notch filtered at 50 Hz. A threshold detection method (mean with 3SD) based on the amplitudes at time window 2,500–500 ms before each stimulus will be set to determine the onset of muscles (40). A positive startle response will be screened out if the onset of either SEM at the time widow of 30–130 ms after stimuli. The positive rate, as well as SEM onset delays (41) will be recorded for analysis.

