A TMS-navigation system (Localite TMS navigator, Germany) will be used to locate the therapeutic targets, record data, and delivery the stimulation. Each patient's MRI data will be collected and imported into the navigation system to build a personalized brain model. Participants will be asked to sit in a comfortable chair with adhesive surface electrodes placed over the muscle belly and tendon of the first dorsal interosseous (FDI). The cortical target eliciting the largest responses and minimum latency of the motor evoked potential (MEP) in the first dorsal interosseous (FDI) muscle at resting status will be determined as the hotspot. The resting motor threshold (rMT) of contralesional hemisphere will be recorded accordingly, which is defined as the lowest stimulus intensity producing a MEP (peak to peak amplitude ≥ 50 μV in at least 5 of 10 trials) in the relaxed condition (30). T.M.S Motor Threshold Assessment Tool (MTAT) 2.0 (http://www.clinicalresearcher.org/software.html) will be used to assess the motor threshold (MT) (31). The location of the FDI hotspot will be set as the cTBS target for cTBS-cM1 group. As to the treatment target for cTBS-cPMA group, the dorsal portion of the superior precentral sulcus (above the superior frontal sulcus) in the contralesional hemisphere will be selected as the landmark for targeting the PMA (32). The sham group will receive cTBS with the same parameters (intensity, time) as the cTBS group on PMA of the unaffected hemisphere but with the coil rotated 90° away from the scalp so that the induced current is minimized. A transcranial magnetic stimulation (TMS MagVenture^®^ MagPro R30, Denmark) with a cool-B65 A/P figure-of-eight-shaped coil will be applied as the stimulator, and the stimulus intensity is set to 70% of contralesional hemisphere's rMT for the three groups. The participants will receive an uninterrupted 40 s train of sham cTBS stimulation over contralesional PMA or an uninterrupted 40 s train of cTBS over contralesional M1 or PMA, respectively. The basic element is a burst ofthree stimuli at 50 Hz, which is repeated at intervals of 200 ms (i.e., 5 Hz) (24), for a total of 600 pulses. Figure 2 shows the cTBS paradigm.

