##### Motor neuron pool excitability: H reflex and M response

Hslp/Mslp (the ratio of the slope of H and M-waves) denotes the relationship between stimulus intensity and motor neuron reflex recruitment (42), and previous researches have proposed Hslp/Mslp and Hmax/Mmax (the ratio of the maximum of H and M-waves) as sensitive and objective measures for the motor neuron pool excitability (42, 43). Poststroke patients have poor autonomic activity, which is thought to contribute to increased reflex excitability manifested by greater Hslp and Hmax on the paretic side (44–46).

A physician will examine all patients with Dantec, two channel EMG. All subjects will be seated comfortably in a chair with their hands resting on thighs and elbows flexed 20°-30°. Paired surface electrodes will be attached to the skin on the belly of the flexor carpi radialis (FCR) muscle. We will stimulate (1 ms duration, once every 3 s) the median nerve at medial to the bicep tendon in the antecubital fossa to elicit H reflexes and M-responses from the flexor carpi radialis muscle. The intensity of these pulses will increase gradually from below the threshold of the H-reflex to supramaximal and saturated condition for M response. At each stimulus intensity, we will deliver 3–5 pulses successively. The H-reflexes and the M responses evoked by these pulses will be amplified in the bandwidth 5 Hz−3 kHz. All amplification procedures are controlled by software running on a signal processor. All signals will be checked and derived to a hard disk for offline analyses. All data regarding the size and series stimulus intensities of both the H-reflex and M response will be used in the construction of the respective recruitment curves and to calculate the average of their maximum values.

Electrophysiological examinations will be performed before and after the first cTBS treatment, at post-intervention (at 4 weeks), and at follow-up (at 8 weeks).

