### Statistical analysis

The SPSS 21.0 program will be used for all statistical analysis and the significance level set for all the analysis will be *P* ≤ 0.05. The Shapiro-Wilk test will be used (*P* > 0.05) to check normality. In this study, Continuous variables will be expressed as mean with standard deviation and median for non-normal distributions and categorical variables will be presented as percentage or frequencies. Between the three groups, data will be first compared using Student's *t*-test for continuous variables and the chi-square or Fisher's exact tests for categorical variables. Appropriate metrics will be processed further using repeated measures ANOVA. Bonferroni correction method and False Discovery Rate <5% will be considered for multiple comparisons. All analyses will be done with the intention to treat principle, and missing data will be estimated using multiple imputation. The mean comparisons for related outcomes in two different moments will be studied with the Wilcoxon-signed rank test. The major strategy for dealing with missing data will be a sensitivity analysis and weighted estimating equations.

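### The immediate startle effect is not tied to an active-versus-sham contrast, and the only test named for two time points is a within-arm test that cannot separate repetition from inhibition by cTBS

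*Protocol article*

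**What the plan says.** The section on the startle reflex describes one run as follows: "the subjects will receive a total of 30 sound stimuli". On the two kinds of sound it adds: "Half of them are 40 ms beeps at 80 dB and half are 40 ms white noises at 120 dB". The spacing is given as "with a random interval of 6–10 s between stimuli to ensure subjects were fully relaxed". Two results are taken from it: "The positive rate, as well as SEM onset delays (41) will be recorded for analysis". That section mentions no familiarisation run, no dropping of early sounds and no adjustment for position in the sequence.

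The timing stands at the end of the H reflex section: "Electrophysiological examinations will be performed before and after the first cTBS treatment, at post-intervention (at 4 weeks), and at follow-up (at 8 weeks"). Table 1 and the Procedure section agree with it. What lies between the first two runs is one session, "an uninterrupted 40 s train of cTBS over contralesional M1 or PMA" or its sham version. All three arms follow the same schedule.

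The Introduction expects cTBS over cPMA to inhibit the overactive medial reticulospinal tract, so fewer or later startle responses would count as support.

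The Statistical analysis section names three tools that could apply:
- a first comparison among the three groups (a t-test for continuous variables, as written);
- repeated measures ANOVA for those metrics that suit it, which are not listed;
- for paired time points: "The mean comparisons for related outcomes in two different moments will be studied with the Wilcoxon-signed rank test".

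It does not say which of these decides the immediate startle effect.

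**The concern.** The before-after startle comparison is a two-time-point outcome, so the Wilcoxon sentence is the one that fits it most directly. A paired test within one arm answers whether the second run differs from the first. It does not answer whether cTBS caused the difference. If responses to loud sounds weaken when the run is repeated, the positive rate falls in every arm, in the direction that the hypothesis predicts.

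Startle is the trial's only electrophysiological measure of the reticulospinal pathway. DTI describes structure and is not taken around the first session. Immediate effects are in the trial's title. If the result is read arm by arm, a significant fall under cPMA stimulation beside a non-significant fall under sham would look like evidence of immediate inhibition, and that pattern can arise without any cTBS effect.

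**Working it through.** **Inputs from the protocol**
- 30 sounds per run, half loud: 30 / 2 = 15 at 120 dB.
- 29 gaps of 6 to 10 s: 29 × 6 = 174 s to 29 × 10 = 290 s per run. The session between the runs lasts 40 s.
- Arm size: 12 per group after dropout. 3 × 12 = 36, and 36 / (1 − 0.20) = 45, or 15 per arm at randomization. This reproduces the plan's total. It was sized on MAS; no figure is given for startle.
- Significance level 0.05, taken as two-sided.

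**Assumptions (not in the documents)**
- Positive rate counted on the 15 loud sounds, with mean 60% before the session.
- Patient rates p vary as a Beta distribution with mean 0.6 and concentration 6.
- Relative habituation h of 0, 10%, 20% or 30%, equal in all arms. The true cTBS effect is zero.

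**Model.** Before-count ~ Binomial(15, p); after-count ~ Binomial(15, (1 − h)p). At h = 20% the mean count falls from 15 × 0.6 = 9.0 to 9.0 × 0.8 = 7.2 in every arm. The active-minus-sham difference is 0.

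**Within one arm.** The first result column gives the share of arms in which the Wilcoxon test is significant, from 5,000 simulated arms per setting.

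**Arm-by-arm reading.** The arms are independent. If q is the chance of a significant fall in one arm, the chance of a significant fall in cPMA but not in sham is q(1 − q). With h = 0, half of the 5% are falls, so q = 0.025. With h of 10% or more, practically all rejections are falls.

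| n per arm | h | Wilcoxon significant in one arm | cPMA yes, sham no: q(1 − q) |
|---|---|---|---|
| 15 | 0 | 5% | 0.025 × 0.975 = 2% |
| 15 | 10% | 25% | 0.25 × 0.75 = 19% |
| 15 | 20% | 67% | 0.67 × 0.33 = 22% |
| 15 | 30% | 95% | 0.95 × 0.05 = 5% |
| 12 | 10% | 19% | 0.19 × 0.81 = 15% |
| 12 | 20% | 58% | 0.58 × 0.42 = 24% |
| 12 | 30% | 87% | 0.87 × 0.13 = 11% |

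The product q(1 − q) cannot exceed 0.25, which it reaches at q = 0.5. Direct simulation of both arms together agrees with the last column to about one percentage point.

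**Between arms.** On the same simulated data (3,000 trials per setting), cPMA against sham is significant in about 4% to 6% of trials at every h. This holds for a t-test on change and for a comparison of after-counts adjusted for before-counts.

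**A second model.** Take normally distributed changes with a drift of 0.25 to 1.0 SD common to all arms. At 15 per arm the within-arm Wilcoxon test shows a significant fall in 14% to 94% of cases. The group-by-time test stays at about 5%.

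**The case against.** A reader might infer that the plan will report habituation as immediate inhibition, or that nothing in the trial removes the order effect. The documents do not support that. The trial is randomized and sham-controlled, and the sham arm hears the same sounds twice. Habituation shared by the arms cancels in any comparison of change between them. The Statistical analysis section does name comparisons between groups and repeated measures ANOVA, and the sample size is set for a within-between effect. The Wilcoxon sentence is generic: it does not mention startle and does not claim to decide anything. A fall in the sham arm would also warn a careful reader.

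The rejection rates of 25% to 95% describe one arm tested alone. They are not the chance of a false claim of efficacy. The closer figure is the 15% to 24% for the mixed pattern at 10% to 20% habituation, and it applies only if the arms are read separately.

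The documents say nothing about habituation or its size. They also do not give the time between the two runs, the order of the electrophysiological tests, or whether the positive rate is counted on 15 or 30 sounds.

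All of this stands, and it limits the point. What it does not supply is the missing commitment. ANOVA is left to unlisted metrics, and the one sentence about paired time points names a test that makes no use of the sham arm. Having a sham arm does not protect separate tests within each arm.

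**Conclusion.** The design can handle repetition effects; the analysis wording does not ensure that it does. With no cTBS effect and assumed habituation of 10% to 30% from a 60% baseline rate, the within-arm test at 15 per arm is significant in about 25% to 95% of cases. The misleading pattern of cPMA significant and sham not reaches about 22% at 15 per arm and 24% at 12, against about 2% without habituation. Comparisons between arms keep close to 5%. These sizes rest on the stated assumptions. The logic needs only that the second run may differ from the first for reasons other than stimulation.

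The point does not show that the trial will misreport its result. It concerns a secondary outcome in a self-described pilot and is worth making because the remedy is cheap. The sham contrast does not solve everything: strong habituation could push the positive rate towards its floor in all arms and reduce sensitivity.

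**What to change.** In the Statistical analysis section, define the immediate startle effect as the active-minus-sham difference in the run after the first session (cPMA versus sham, and cM1 versus sham), adjusted for the patient's own run before it. State that within-arm Wilcoxon results are descriptive and support no claim of inhibition. The same sentence can cover the other measures taken around the first session.

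A model at the level of single sounds, with position in the sequence and a patient effect, is optional; it is not needed to remove an order effect that all arms share.

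The change needs no new visits, patients or measurements. The cost is precision: a difference between two equal arms has a standard error √2 ≈ 1.41 times that of one arm's change, before any gain from adjusting for the first run.

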##### Motor neuron pool excitability: H reflex and M response

Hslp/Mslp (the ratio of the slope of H and M-waves) denotes the relationship between stimulus intensity and motor neuron reflex recruitment (42), and previous researches have proposed Hslp/Mslp and Hmax/Mmax (the ratio of the maximum of H and M-waves) as sensitive and objective measures for the motor neuron pool excitability (42, 43). Poststroke patients have poor autonomic activity, which is thought to contribute to increased reflex excitability manifested by greater Hslp and Hmax on the paretic side (44–46).

A physician will examine all patients with Dantec, two channel EMG. All subjects will be seated comfortably in a chair with their hands resting on thighs and elbows flexed 20°-30°. Paired surface electrodes will be attached to the skin on the belly of the flexor carpi radialis (FCR) muscle. We will stimulate (1 ms duration, once every 3 s) the median nerve at medial to the bicep tendon in the antecubital fossa to elicit H reflexes and M-responses from the flexor carpi radialis muscle. The intensity of these pulses will increase gradually from below the threshold of the H-reflex to supramaximal and saturated condition for M response. At each stimulus intensity, we will deliver 3–5 pulses successively. The H-reflexes and the M responses evoked by these pulses will be amplified in the bandwidth 5 Hz−3 kHz. All amplification procedures are controlled by software running on a signal processor. All signals will be checked and derived to a hard disk for offline analyses. All data regarding the size and series stimulus intensities of both the H-reflex and M response will be used in the construction of the respective recruitment curves and to calculate the average of their maximum values.

Electrophysiological examinations will be performed before and after the first cTBS treatment, at post-intervention (at 4 weeks), and at follow-up (at 8 weeks).

#### Neuroimaging: diffusion tensor imaging

Diffusion Tensor Imaging (DTI) will be evaluated at baseline and after the 4-week treatment. And it will be conducted as follows. All individuals will be subjected to 3.0 T MRI scanner (Discovery LS MR 750; GE Healthcare, Chicago, IL, USA) equipped with a 16-channel head & neck coil to acquire 3D T1-weighted and DTI images before and after 20 times therapy.

DTI is used in diffusion-weighted gradients along 60 non-collinear directions and two non-diffusion-weighted volumes. Scanning parameters will include matrix size = 128 × 128, field of view = 230 × 230 mm^2^, TR = 5,800 ms, TE = 71 ms, flip angle = 180°, number of averages = 1, b value = 1,000 s/mm^2^, slice thickness = 4 mm, and voxel size = 1.7 × 1.7 × 4 mm^3^ (47).

DTI data processing will be carried out as follows. (1) Normalization: All data will be spatially normalized using parameters derived from 3D T1WI processing. We will use FMRIB's Diffusion Toolbox and TBSS (Tract-Based Spatial Statistics) (both from the FMRIB Software Library 6.0, FSL, https://fsl.fmrib.ox.ac.uk/fsl/fslwiki/FSL) to analyze DTI data. (2) Registration: We will use FSL tools to get the transformation matrix and then correct the eddy current distortions in the DTI datasets. After that, each subject's raw diffusion-weighted pictures will be linearly aligned to a non-diffusion weighted image (b0) with the removal of the non-brain tissues using a brain extraction tool (BET). (3) Local fitting: The extracted brain will be used for diffusion tensors. The diffusion tensor will be estimated at each voxel to obtain the fractional anisotropy (FA) pictures (47). We will select the region of interest (ROI) method to measure tract integrity. The red nucleus (RN) is an appropriate part to draw ROI (7). We will draw ROI on the posterior limb of internal capsule and the anterior pons on a color-coded map for CST and on the RN for RST individually. In each ROI, we will extract fractional anisotropy (FA), mean diffusivity (MD), radial diffusivity (RD) and axial diffusivity (AD). Three dimensional reconstructions of the CST and RST will be performed for each patient.

DTI has been commonly used to quantitatively measure the integrity of tissues. Previous studies reported the DTI biomarkers (e.g., FA) measured after stroke have emerged as potential predictors of motor recovery (48, 49).

### Sample size calculation

Sample size is estimated through software G^*^Power 3.1 (50). We used MAS as the primary outcome for the calculation of the effect size. It is determined to be 12 per group based on a power of 0.8 with α level at 0.05. According to a previous study (21), effect size *d* = 0.53 was calculated based on the difference in MAS score from their main research results. Through conversion, the effect size *f* used in our study is about 0.25. Repeated measures correlation in our study is set at 0.5 to detect a moderate within-between effect of Conhen's *f* = 0.25. Considering a drop-out rate of 20%, we aim to recruit totally 45 stroke subjects.

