Limited interventions were proven effective currently in improving spasticity. The only botulinum toxin injection backed by a lot of evidence is expensive and may require multiple iterations (16). Some central modulating strategies have also been attempted to treat post-stroke spasticity. Transcranial magnetic stimulation (TMS) is one of the options. However, ambiguity in research results leads to the disapproval of this technology on post-stroke spasticity (17, 18). The reason for this may be that previous study designs did not take into account the dynamic reorganization of CST/RST, and mainly focused on the promotion of motor recovery (1). Almost all studies with positive results were interventions targeting the bilateral M1 areas (part of CST) (19–21), improvement in spasticity accompanied by significant motor recovery. This can be interpreted as a weakening of RST regulation by enhancing CST control, which may not the most direct way to regulate spasticity-related pathways. Moreover, the traditional inhibitory TMS therapy developed based on the theory of hemispheric inhibition (22) was insufficient to reverse cortical excitability in all subjects or produced short-lived or variable results (23). Continuous theta burst magnetic stimulation (cTBS) is a novel patterned protocol of TMS, it can induce long-term depression (LTD) effect on cortical excitability and lead to long-term therapeutic benefits in facilitating induction of neuronal plasticity mechanisms (24). TBS has the advantages of shorter stimulation duration, low stimulation pulse intensity, longer post-acting time, and probably improved efficiency compared with ordinary rTMS, which is regarded as a very promising therapy (25). In addition, how to assess post-stroke spasticity objectively also set a barrier for related research. Most previous studies of TBS on post-stroke spasticity mainly use the modified Ashworth scale (MAS) as their primary outcome (18), which only roughly reflects changes in spasticity, and does not benefit mechanistic exploration.

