### Outcome measurements

The primary outcomes are MAS and FMA-UE. Changes before and after the 4 weeks of treatment will be used as the primary measure to assess improvement in spasticity and abnormal movement synergies (9). And the secondary outcomes are results from neurophysiological examinations including H reflex, M response, MEP and SR, and changes of neuroimaging with DTI.

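### The 80% power claim uses an interaction f of 0.25 that does not follow from the cited d of 0.53; if d is a between-arm difference, power is about 18–29% at the plan's own correlation

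*Protocol article*

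**What the plan says.** All inputs stand in the Protocol article, mostly under Sample size calculation.

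- Outcome: "We used MAS as the primary outcome for the calculation of the effect size".
- Source: "effect size *d* = 0.53 was calculated based on the difference in MAS score from their main research results".
- Conversion: "Through conversion, the effect size *f* used in our study is about 0.25". No formula is given.
- Test sized: "Repeated measures correlation in our study is set at 0.5 to detect a moderate within-between effect of Conhen's *f* = 0.25".
- Result: "It is determined to be 12 per group based on a power of 0.8 with α level at 0.05". With 20% drop-out this becomes 45 recruited.

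The number of visits in the calculation is not stated. Table 1 schedules the MAS at baseline, week 4 and week 8. Outcome measurements narrows the primary measure: "Changes before and after the 4 weeks of treatment will be used as the primary measure". Study design calls the trial a pilot. The Discussion part of the Abstract, and the Discussion itself, nevertheless expect the results to give strong support for using the treatment.

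**The concern.** A standardised difference d and an interaction f are on different scales. A one-way f is the spread of the group means at one time point. An interaction f is the spread of the group-by-time effects over all cells, after the group and time averages are removed. Randomised arms are equal in expectation at baseline, so part of any post-treatment difference goes into the group average and less remains as interaction. If a one-way f is entered in the interaction field, the software also multiplies it by the gain from repeated measures, and the required sample comes out too small.

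A reader of this section would take the trial to have an 80% chance of detecting the effect seen in the earlier study. If the conversion is wrong, the chance is far lower, and a non-significant result would say little about an effect of that size.

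**Working it through.** **Inputs from the article.** d = 0.53, f = 0.25, correlation ρ = 0.5, α = 0.05, k = 3 groups, 12 per group (N = 36), 20% drop-out, MAS at three visits.

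**1. Reproducing the plan's figure.** For the within-between interaction with m visits, λ = f²·N·m/(1−ρ), df₁ = (k−1)(m−1), df₂ = (N−k)(m−1).

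- m = 3, N = 36: λ = 0.0625 × 36 × 3/0.5 = 13.5, df 4 and 66, power 0.823.
- m = 3, N = 33: power 0.781.
- Drop-out: 36/0.8 = 45.

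So 12 per group and 45 in total follow from f = 0.25 with three visits.

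**2. Where 0.25 could come from.** Two one-way formulas land near it: d/2 = 0.265 for two groups, and d·√2/3 = 0.250 when one of three arms differs. Both describe a single time point. The article does not say which was used, if either.

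**3. The interaction f that matches d = 0.53.** Assume arms equal at baseline and a difference of 0.53 single-visit SDs afterwards, held to week 8. Then f = d × (RMS of the centred group pattern) × (RMS of the centred time pattern), where RMS is the root mean square.

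- Group pattern: one arm differs (0, 0, 1), √2/3 = 0.471; graded (0, ½, 1), √(1/6) = 0.408.
- Time pattern: two visits (0, 1), 0.5; three visits (0, 1, 1), √2/3 = 0.471.

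| Pattern | f | Power, 12 per group | Power, 15 per group |
|---|---|---|---|
| One arm, two visits | 0.53 × 0.471 × 0.5 = 0.125 | 0.231 | 0.285 |
| One arm, three visits | 0.53 × 0.471 × 0.471 = 0.118 | 0.229 | 0.285 |
| Graded, two visits | 0.53 × 0.408 × 0.5 = 0.108 | 0.182 | 0.222 |
| Graded, three visits | 0.53 × 0.408 × 0.471 = 0.102 | 0.178 | 0.219 |

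Example: one arm, two visits, N = 36 gives λ = 0.1249² × 36 × 2/0.5 = 2.25 with df 2 and 33. If both active arms differ equally from sham, the figures are those of the one-arm rows.

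**4. Cross-check by pairwise t-test on change.** At ρ = 0.5 the SD of change is √(2(1−0.5)) = 1 single-visit SD, so d stays 0.53. The noncentrality is 0.53 × √(12/2) = 1.30, power 0.237; with 15 per group it is 1.45, power 0.289. For 80% power, 57 per group are needed. The interaction test with one arm differing needs 49 (three visits) or 53 (two visits).

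**5. Sensitivity to ρ.** Over the same patterns and both group sizes, power is about 14–21% at ρ = 0.3 and 28–46% at ρ = 0.7.

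**6. What f = 0.25 means as a difference.** Scaling step 3, 0.53 × 0.25/0.125 is about 1.06 SD (one arm, two visits) and 0.53 × 0.25/0.102 is about 1.30 SD (graded, three visits). That is at least twice the cited effect.

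**7. Number of visits.** Granting f = 0.25 but using two visits, to match the baseline-to-week-4 change: N = 36 gives λ = 9.0 and power 0.73; N = 42 gives 0.80; N = 45 gives 0.83. With 36 completers, 80% power needs f of about 0.27, or about 1.15–1.3 SD.

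**The case against.** The strongest reply is that the documents do not establish what d is. The article mentions a difference in MAS score but not whether it lies between arms or before and after treatment, nor which SD was used, and the source study is not at hand. This stands, so the percentages are conditional. It does not rescue the plan: a before-after d within one arm would not measure a between-group effect at all.

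Four stronger readings are tempting and not supported.

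- **That the authors simply halved d.** The article shows no conversion, and d·√2/3 = 0.250 fits the stated value better than d/2 = 0.265. What can be said is that the value fits a one-way f.
- **That the sample-size arithmetic is wrong.** It is not. From f = 0.25 onwards every figure reproduces; the input is at fault.
- **That power is one firm low number.** It depends on the pattern of means and on ρ, and adjusting for baseline would raise the t-test figures to about 30–37% at ρ = 0.5. No value examined comes near 80%.
- **That power for premotor versus M1 stimulation can be computed.** The article gives no effect for that contrast. The Introduction cites the source study in support of this sentence: "Almost all studies with positive results were interventions targeting the bilateral M1 areas". An effect of M1 stimulation does not size a comparison between the two active targets, and any figure for it would be an assumption.

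On visits, three MAS assessments and a planned repeated measures ANOVA make m = 3 a natural choice, and intention to treat with multiple imputation places two-visit power at f = 0.25 between 0.73 and 0.83. The visit mismatch is therefore the lesser point. The pilot label is fair context, but the article still claims formal 80% power.

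**Conclusion.** The concern holds in a conditional form. The stated 80% power belongs to an interaction f of 0.25, and that f does not follow from d = 0.53 by any route the article shows. If d is a between-arm difference in single-visit SD units, with arms equal at baseline, power at the plan's ρ = 0.5 and α = 0.05 is about 18–24% with 12 per group and 22–29% with all 15. The exact percentages depend on the pattern of means and on ρ; the conclusion that power is far below 80% holds for ρ from 0.3 to 0.7. Separately, the calculation reproduces only with three visits, while the primary measure uses two.

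**What to change.** Keep 45 patients and rewrite the Sample size calculation paragraph.

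- State how d = 0.53 was defined (between arms or before-after, which SD, which time point) and how it was converted.
- State the number of visits, and make it match the primary measure in Outcome measurements.
- Give the effect detectable with 80% power for the design chosen. With 36 completers this is f = 0.25 for the three-visit interaction (about 1.1–1.3 SD), or f of about 0.27 for two visits (about 1.15–1.3 SD). The three-visit sentence must not be kept if the two-visit measure is adopted.
- Say that power for d = 0.53 is roughly 18–29% at ρ = 0.5, and drop the 80% claim for the cited effect.
- Keep the pilot label, report premotor versus M1 stimulation as an estimate with a confidence interval, and soften the strong-support wording in the Abstract and Discussion.

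The cost is some rewording and a less favourable stated figure. No extra patients, visits or assessments are needed.
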